#### Control: care as usual

The intervention will be compared to a control group, which is care as usual. In this group, participating GPs will not receive the training or the conversation guides, and patients will not receive the workbook developed for the intervention. The control group will also not feature the two planned consultations dedicated specifically to discussing ACP as included in the intervention arm. Participating patients will consult with their GP as they usually do. During these consultations, the topic of ACP may still spontaneously be addressed, either by the GP or patient. Other already-available national documents, such as advance directive forms or patient guide materials, may be used as the GP or patients see fit.

#### Criteria for discontinuing or modifying allocated interventions for a given trial participant

Participants may discontinue their participation at any time and for any reason, as is described in the informed consent forms. Patients will be monitored by the researchers for the possibility of adverse events and may discontinue their participation in response to adverse events, the detection of which will prompt a notification of the trial manager and the ethics committee.

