**Table Taba:** 

(1) To **test** the effectiveness of the ACP-GP intervention on: • the patient’s level of engagement with ACP (primary outcome at patient level) • the GP’s self-efficacy for conducting ACP (primary outcome at GP level) (2) To **explore** the effect of the ACP-GP intervention on: • patient quality of life; symptoms of anxiety; symptoms of depression; the appointment of a substitute decision-maker; completion of new ACP documents; thinking about ACP, and communication with the GP (secondary outcomes at patient level) • GP ACP practices, attitudes and knowledge about ACP, and the documentation of ACP discussions in the patient medical file (secondary outcomes at GP level) • the SDM’s level of engagement with ACP (secondary outcome at the SDM level) (3) To **evaluate** the recruitment and implementation process of the intervention in terms of its reach, efficacy, adoption, implementation, and maintenance; as reported by patients, their SDM if present, and GPs	

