### Outcomes

#### Study endpoints and assessments

This study uses both qualitative and quantitative data to measure the outcomes of the intervention. As the intervention consists of components developed for the GP and patient, outcomes will be measured at both levels. The primary and secondary outcomes are listed in Table 3.

**Table 3 Tab3:** Outcomes, measurement instruments and timing

	Measurement tool	Completed by	Timing of measurement		
Primary outcome			T0	T1	T2
Level of engagement with ACP	*ACP Engagement Survey 15-item version* [24] • Reported on an overall average 5-point Likert scale (range 1–5)	Patient	X	**X**	X
ACP Self-efficacy	*ACP Self-efficacy Scale (ACP-SE)* [25] • 17 items • Reported on an overall average 5-point Likert scale (range 1–5) • 1 additional general item including all advance care planning can be used for comparison to the scale	GP	X	**X**	X
Secondary outcomes					
Health-related quality of life	*Short Form Health Questionnaire (SF-12v2)* [26] • Physical Health (PCS) and Mental Health (MCS) summary scores (range 0–100)	Patient	X	X	X
Anxiety	*Generalized Anxiety Disorder Questionnaire (GAD-7)* [27] • Sum score (range 0–21)	Patient	X	X	X
Depression	*Patient Health Questionnaire (PHQ-9)* [28] • Sum score (range 0–27)	Patient	X	X	X
Appointment of a substitute decision maker	GP report ACP engagement survey “readiness to sign official papers assigning a SDM” item	Patient GP	X	X	X
Completion of new ACP documents	Patient report GP report ACP engagement survey “readiness to sign official papers stating medical wishes” item	Patient		X	X
Thinking about ACP	1 self-developed item, 10-point Likert (“How much have you thought about ACP in the last 3 months?”; response categories range from “not at all” to “very much”)	Patient	X	X	X
Communication with the GP	4 self-developed items, 10-point Likert (e.g., “To what extent did the GP listen to your concerns about your future health?”; response categories range from “not at all” to “very much”)	Patient	X	X	X

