#### Harms

The ACP intervention is a non-invasive intervention, focused on conversations between GPs, patients, and SDMs regarding values and wishes for future medical care. Previous research has shown that people with life-limiting illnesses see participating in research such as this study as a worthwhile endeavor [17]. Adverse effect from participating in similar research, as may be implied by dropout due to the subject being too psychologically taxing to talk about, are rare [33]. However, people living with chronic life-limiting illnesses are a vulnerable group for whom the appropriate concern and ethical measures must be in place. An anticipated adverse event which may arise during the intervention is mild psychological discomfort in participating patients and SDMs, which may be caused by some questions in the ACP Engagement Survey or the workbook, or as a result of ACP conversations with the GP. However, participants will be informed of their right to refuse to answer any question and that they may withdraw from the study at any time without negative consequence. The possibility of a patient or SDM becoming distressed during the ACP discussions will be discussed during the GP training.

As the study involves patients with a chronic, life-limiting illness, it is possible that some patient drop-out is due to death related to disease progression, but this would not be related to the study protocol. A bereavement protocol has been established for the SDM if the patient dies during the study period. If researchers are informed that a patient has died, this will be communicated to the ethics committee. The bereaved SDM will be contacted with condolences and, if necessary, will receive information to refer them to appropriate support resources.

While the investigators cannot predict the occurrence of unanticipated or unexpected adverse events, we do not anticipate any serious adverse events associated with the research protocol. Nevertheless, we have included measures to detect increases in anxiety and depression at T1 and T2 and will act accordingly in the case of adverse events. These will be reported to the principal investigator and forwarded to the ethics committee. In the case of an adverse event involving a patient, the GP and specialist health provider to the patient will be notified if necessary.

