#### Ancillary and post-trial care

In the case of an adverse event for a patient during the study, the GP and, if necessary, the specialist health provider to the patient will be notified to further refer the patient to existing medical care services. The researchers will also be available to refer patients and SDMs to appropriate supportive resources based on needs identified during the study.

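### The plan expects distress in patients and surrogate decision makers (SDMs) alike, but monitors and measures it in patients only, so SDM harm rests on unsystematic report that is uneven between arms

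*Protocol article*

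**What the plan says.** The Harms section anticipates "mild psychological discomfort in participating patients and SDMs" and gives its sources: "which may be caused by some questions in the ACP Engagement Survey or the workbook, or as a result of ACP conversations with the GP". Two paragraphs later it says "we have included measures to detect increases in anxiety and depression at T1 and T2".

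The section on criteria for discontinuing or modifying allocated interventions first gives all participants the right to stop, then narrows to patients: "Patients will be monitored by the researchers for the possibility of adverse events".

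The Objectives table places "patient quality of life; symptoms of anxiety; symptoms of depression" among the patient-level secondary outcomes. Table 3 lists the GAD-7 and PHQ-9 as completed by the patient at T0, T1 and T2. The one outcome instrument completed by SDMs is the 17-item SDM version of the ACP Engagement Survey, whose domains concern serving as SDM, contemplation and readiness.

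Under Ancillary and post-trial care, the researchers will be available to "refer patients and SDMs to appropriate supportive resources based on needs identified during the study". The process evaluation part of Table 3 lists reported adverse effects under the efficacy/effectiveness domain.

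**The concern.** The plan names two groups in whom it expects discomfort. Its stated active monitoring and its symptom scales reach only one of them. Table 3 assigns each instrument to a respondent and the monitoring sentence names its target, so this is a scope the document states, not detail lost in condensing.

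Two things are at stake. First, adverse effects are to be reported as part of the effectiveness picture. If SDMs are not asked systematically, a count of few or no SDM events could be taken as evidence of no harm. Second, most routes by which SDM distress could come to light run through the intervention arm, so any difference in reports between arms would mix harm with ascertainment. The referral offered to SDMs also depends on needs being noticed first.

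**Working it through.** **Number of SDMs (Sample size section).** 18 GPs per group × 3 patients × at most 1 SDM = 54 per group, and 54 × 2 = 108. This reproduces the plan's figure. It is a maximum, because a patient may take part without naming an SDM.

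**Exposure by source of discomfort.**
- Engagement survey: both arms, so up to 108 SDMs.
- Planned ACP conversations: intervention arm only, so at most 54, and SDM attendance is the patient's choice (Table 2).
- Workbook: given to intervention patients and withheld from controls, so any SDM exposure is indirect and limited to the same 54.

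**Ascertainment, side by side.**

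| Element | Patients | SDMs |
|---|---|---|
| Named as likely to have discomfort (Harms) | Yes | Yes |
| Active adverse-event monitoring stated | Yes | Not stated |
| GAD-7 and PHQ-9 | T0, T1, T2 | None |
| T1 questionnaire on conversations | Yes | None listed |
| T1 satisfaction questionnaire | Yes, intervention arm | None listed |
| Referral to support | Yes | Yes, once a need is identified |

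**Routes by which SDM distress could still surface.**

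| Route | Arms |
|---|---|
| Approach by the research assistant at T1; questionnaire support at T0 and T1; telephone follow-up at T2 | Both |
| GP training that covers SDM distress during conversations | Intervention during the trial (controls are offered training afterwards) |
| Trainer check-ins with GPs on delivery and problems | Intervention |
| Audio-recordings of ACP conversations, with the SDM if present | In effect intervention, where the planned conversations take place |
| 10–15 interviews after the 6-month period | Intervention |

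Reporting any adverse event to the ethics committee and referring SDMs to support apply in both arms, but both act only after an event is known. The bereavement protocol is triggered by the patient's death, not by the anticipated discomfort.

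**Reach of the interviews.** If every interview included an SDM, 10/54 = 18.5% to 15/54 = 27.8% of the maximum number of intervention SDMs would be covered. Of all 108 the share is 10/108 = 9.3% to 15/108 = 13.9%. No control SDM is included.

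**What asking everyone would buy.** Suppose all 54 intervention SDMs were asked and none reported distress. The one-sided 95% upper limit on the rate would be 1 − 0.05^(1/54) = 1 − 0.946 = 0.054, or 5.4%. This assumes all 54 exist, all answer, and responses are independent within GP; fewer respondents would raise the limit. With spontaneous report there is no denominator of people asked. A limit would then need the share of cases that get reported, which the document does not give.

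**The case against.** The strongest reply is that SDMs are not forgotten. Research staff contact them at T1, they can have help with the T0 and T1 forms, GPs are trained to expect their distress, adverse events are reportable whoever they concern, and referral and bereavement provisions name them. This stands. A reader might infer that SDM harm could be found only by chance, or that nothing in the plan would identify it. The document does not support that, because there are planned routes. They are unsystematic and, for the most part, one-sided.

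A reader might also infer that the Harms section wrongly claims the anxiety and depression measures cover SDMs. It does not. That sentence sits in a later paragraph on unanticipated and serious events and never says who completes the scales. For mild discomfort the section relies on the right to refuse questions, the right to withdraw, and GP training. These may protect participants, but they do not record whether distress occurred.

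Third, the article is condensed and the questionnaires are available only on request, so it cannot be shown that SDMs will never be asked. That is fair, and the point is confined to the scope the article states. It is also defensible not to give relatives a symptom scale when only mild discomfort is expected. The remedy below does not ask for one.

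Finally, a question about the workbook or the conversations could reveal allocation to the blinded data collector at T1, when the primary outcomes are measured. This is a sound objection to such wording, and the fix avoids it.

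**Conclusion.** The point holds. The plan anticipates discomfort in SDMs but describes no systematic way of ascertaining it. Its stated monitoring and both symptom scales are limited to patients. Up to 108 SDMs face the survey, and at most 54 could attend planned conversations. Few SDM reports could not be taken as absence of harm, and a comparison of SDM reports between arms would be confounded by unequal ascertainment.

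The conclusion rests on the scope as written in the article and on the maximum SDM count; actual numbers may be lower. No rate of undetected distress is claimed. The primary outcomes and their analysis are unaffected. The anticipated event is mild, so this is a change that should be made, not one that puts the trial's main conclusions in doubt.

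**What to change.** 1. Reconcile the monitoring sentence in the discontinuation section with the Harms and Ancillary care sections, so that monitoring covers patients and SDMs.
2. State in the Harms section that the GAD-7 and PHQ-9 cover patients only.
3. Add one neutral question on distress from taking part in the study to the self-completed SDM form at T1 and T2, worded identically in both arms. It should not mention the workbook or the conversations, so that the blinded data collector is protected.
4. Report the answers by arm, with the number of SDMs who answered as the denominator.

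The cost is one item on forms SDMs already complete and a few sentences in the protocol. The downside is slightly more SDM burden and probably more mild events reported.

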### Relevant concomitant care and interventions that are permitted or prohibited during the trial

There are no restrictions regarding concomitant medical care or medical interventions during the trial period. Participants may receive care as normal, with the exception of participation in other studies or trials evaluating ACP interventions, palliative care services, or other communication strategies. Patients participating in such studies or trials will be excluded from participating in this study.

### Outcomes

#### Study endpoints and assessments

This study uses both qualitative and quantitative data to measure the outcomes of the intervention. As the intervention consists of components developed for the GP and patient, outcomes will be measured at both levels. The primary and secondary outcomes are listed in Table 3.

**Table 3 Tab3:** Outcomes, measurement instruments and timing

	Measurement tool	Completed by	Timing of measurement		
Primary outcome			T0	T1	T2
Level of engagement with ACP	*ACP Engagement Survey 15-item version* [24] • Reported on an overall average 5-point Likert scale (range 1–5)	Patient	X	**X**	X
ACP Self-efficacy	*ACP Self-efficacy Scale (ACP-SE)* [25] • 17 items • Reported on an overall average 5-point Likert scale (range 1–5) • 1 additional general item including all advance care planning can be used for comparison to the scale	GP	X	**X**	X
Secondary outcomes					
Health-related quality of life	*Short Form Health Questionnaire (SF-12v2)* [26] • Physical Health (PCS) and Mental Health (MCS) summary scores (range 0–100)	Patient	X	X	X
Anxiety	*Generalized Anxiety Disorder Questionnaire (GAD-7)* [27] • Sum score (range 0–21)	Patient	X	X	X
Depression	*Patient Health Questionnaire (PHQ-9)* [28] • Sum score (range 0–27)	Patient	X	X	X
Appointment of a substitute decision maker	GP report ACP engagement survey “readiness to sign official papers assigning a SDM” item	Patient GP	X	X	X
Completion of new ACP documents	Patient report GP report ACP engagement survey “readiness to sign official papers stating medical wishes” item	Patient		X	X
Thinking about ACP	1 self-developed item, 10-point Likert (“How much have you thought about ACP in the last 3 months?”; response categories range from “not at all” to “very much”)	Patient	X	X	X
Communication with the GP	4 self-developed items, 10-point Likert (e.g., “To what extent did the GP listen to your concerns about your future health?”; response categories range from “not at all” to “very much”)	Patient	X	X	X
ACP Practices	• *Next Steps training program questionnaire* [29] (4 items) • 2 items specific to practices with patients with chronic, life-limiting illness (“Which percentage of your patients has a chronic, life-limiting illness” and “With which percentage of your patients with a chronic, life-limiting illness do you conduct ACP conversations?”; 4 response options per item) [25] • 8 additional items regarding ACP practices (e.g., “Where do the ACP conversations you conduct usually take place?”)	GP	X	X	X
ACP Attitudes	*Next Steps training program questionnaire* [29] • 9 items; 5-point Likert scale ranging from “Completely disagree” to “Completely agree”; adapted to the Belgian legal context	GP	X	X	X
ACP Knowledge	*Next Steps training program questionnaire* [29, 30] • 10 items; correct/not correct/don’t know; adapted to the Belgian legal context	GP	X	X	X
Documentation of ACP discussion outcomes	Documentation template review	GP		X	X
Level of engagement with ACP	*ACP Engagement Survey, substitute decision maker version* [31] • 17 items; 5-point Likert scales • 3 domain scores (“Serving as SDM”, “Contemplation”, Readiness”) computed as the unweighted average of items per domain (range 1–5)	SDM	X	X	X
Other measurements					
Demographic information	For patients and surrogate decision makers: • Gender • Age • Marital status • Highest completed education • Religion • Patient/SDM relationship • Whether patient and SDM live together or apart For patients: • Previous completion of any advance directives (“wilsverklaringen”) For surrogate decision makers: • How long they have known the patient For GPs: • Gender • Age • Graduation year • Practice setting(s) • Years of experience as a GP • Graduating university • Working in a palliative home care team (yes/no) • Working as a “coordinating and advising practitioner” in a residential care facility (yes/no) • Prior formal ACP education or training (intensive/introductory/none) • Prior formal palliative care education or training (intensive/introductory/none)	GP Patient SDM	X		
Process evaluation					
**RE-AIM domain**	**Operationalization**	**Measurement**			
**Reach**	• Comparing the characteristics of participating patients with non-participants	• Documentation of the recruitment process by the researchers • Documentation of reasons given for not participating • Participant demographics			
**Efficacy/effectiveness**	• Primary and secondary outcomes of the RCT	• See primary and secondary outcomes above • Reports of any adverse effects			
**Adoption**	• ACP discussion documents uploaded • Patient use of the work booklet • Experiences of GPs and patients applying intervention steps • Changes in GP practice	• Training topic checklist (after each training) • Questionnaire for GPs regarding their ACP practices and conversations in the last 3 months (T1) • Questionnaire for patients regarding ACP conversations with their GP in the last 3 months (T1) • Documentation template review (T1, T2) • Contents of work booklet from a sample of patients in the intervention group (physical copy or digital scan) (T1, T2) • Check-in discussions between GPs and trainers (continuous) • Focus groups with GPs (after T2) • Semi-structured interviews with patients and SDM (after T2)			
**Implementation**	• Fidelity: the extent to which the steps of the intervention were followed as specified in the protocol • Patient and GP barriers/facilitators to following the steps of the intervention • Satisfaction of GPs and patients with the intervention components	• Training topic checklist (after each training) • Check-in discussions between GP and trainers (continuous) • Audio recordings of ACP consultations between GP and patient (and SDM if present) • Documentation template review (T1, T2) • Satisfaction questionnaire for intervention GPs and patients (T1) • Focus groups with GPs (after T2) • Semi-structured interviews with patients and SDM (after T2)			
**Maintenance**	• GP intention for using the intervention materials in the future • Recommendations by the GP and patients to improve intervention usability in the future	• Satisfaction questionnaires for intervention GPs and patients (T1) • Focus groups with GPs (after T2) • Semi-structured interviews with patients and SDM (after T2)			

We have two separate primary outcomes, one at the GP level and one at the patient level. Success on any one of these outcomes at T1 may support a conclusion of effectiveness. Hence there are several ways for the study to successfully demonstrate a treatment effect. This multiplicity problem has been taken into account in the power analysis by controlling the Type I error rate at 2.5% (Bonferroni method).

Scores on the ACP Engagement Survey and the ACP Self-Efficacy Scale for GPs will also be measured at T2. We will treat T2 scores on these scales as a secondary outcome.

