## Background

Advance Care Planning (ACP) refers to “a process that supports adults at any age or stage of health in understanding and sharing their personal values, life goals, and preferences regarding future medical care” [1]. This may include the completion of a living will or Advance Directive (AD), which document wishes for future care should patients be unable to make their wishes known due to declining health or incapacity; and/or the appointing of a surrogate decision-maker (SDM), who can make care decisions in the place of the patient if the patient is unable to speak for themselves. ACP can lead to greater concordance between care preferences and care received [2], improved communication about the end of life with care providers [3], greater satisfaction with physician visits [4], and improved quality of end-of-life care [5]. It is a prerequisite for a good coordination of care, including palliative and end-of-life care, by making clear which medical decisions will be considered appropriate when the patient is unable to make such a decision themselves [6].

For patients with chronic, life-limiting illness (es), which are often marked by trajectories of steady illness progression or gradual health decline punctuated by acute deterioration [7], it is important that ACP is initiated in a timely manner so that sufficient time can be dedicated to conversations about values, goals and preferences [8]. ACP is intended as a continuous process of communication. For patients, engaging in ACP is not an isolated occurrence [9], but a complex behavior where readiness to engage in discrete behavior is an important precursor to action [10]. Especially suited to initiating these interactive discussions over multiple visits is the general practice setting. In Belgium, as in many other European countries, general practitioners (GPs) observe the patient’s health over the course of regular visits, often have a trusting relationship with the patient, and often are aware of the patient’s medical and social context [11, 12]. However, while the role of the GP in initiating ACP conversations is highlighted in guidelines of care [13], currently the process of ACP between patients and GP is not often initiated [14].

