### Intervention and control

#### Intervention

The ACP-GP intervention (Table 2) is designed to 1) train GPs to conduct ACP discussions with eligible patients, 2) prepare patients for the conversation by providing them with a workbook about ACP, 3) facilitate at least 2 ACP conversations between GP and patient (and SDM if present), and 4) document the outcomes of the discussion in the patient electronic medical file with the help of a structured template.

**Table 2 Tab2:** Key elements of the ACP-GP intervention

1. GP training	The GP training, which has been tested multiple times, is originally conceptualized as two interactive sessions of 3 h each, delivered to small groups of 6–8 GPs at a time within the university hospital setting or another location that is convenient for the participants. However, due to COVID-19 concerns, the content of the training has been translated to an online platform. The training is provided by a trainer experienced in primary care and communication. Two interactive web sessions of approximately 2 h each will replace the live sessions. Preparatory activities such as fictional case examples with reflection questions will be available before the training begins. GPs will have access to background information portions through an e-learning module presented via the Ufora platform of the Universiteit Gent. This module will take no more than 60 min to review. The first aim, improving ACP knowledge, will be addressed via the e-learning module. ACP communication skills will be practiced with video role-modeling exercises which are available on the e-learning module and will be further elaborated on during the web sessions. These web sessions will also include role-play exercises with model patients and interactive discussions with fellow GPs and the trainer. During the training, GPs will receive an extensive conversation guide and an at-a-glance conversation flowchart. These can be used as preparation for and during ACP conversations with patients. In the context of their continuous medical education, GPs will be able to obtain accreditation in ethics and economy by following the training. GPs in the control group will have the opportunity to follow the training after the conclusion of the study, so that both groups have access to this incentive. After the training sessions, GPs will have the opportunity for check-in discussions with the trainers to ask questions and report issues.

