#### SDMs

RA’s will assist patients with identifying a SDM using a pre-written script which asks whether the patient has formally appointed someone, and if not, who may be able or willing to fulfill this role. If the SDM is present at the time of the visit, they will be asked if they would like to participate. If the SDM is not present, the researchers will ask permission from the patient to contact them regarding the study. If such a person wishes to participate, they will also be asked to provide informed consent.

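### SDM appointment is measured by GP report and a readiness item, with no direct patient report, so ascertainment is likely to be more complete in the intervention arm

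*Protocol article*

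**What the plan says.** The Objectives list, among the secondary patient outcomes to be explored, "the appointment of a substitute decision-maker; completion of new ACP documents". These are two separate outcomes, and each is something that has or has not happened.

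Table 3 (Study endpoints and assessments) gives their sources:

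- Appointment of an SDM: "GP report ACP engagement survey “readiness to sign official papers assigning a SDM” item", at T0, T1 and T2, completed by patient and GP.
- Completion of new ACP documents: "Patient report GP report ACP engagement survey “readiness to sign official papers stating medical wishes” item", at T1 and T2.

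The second row names a patient report; the first does not, and its only patient-side source is the item on "readiness to sign official papers assigning a SDM". The Background describes how "readiness to engage in discrete behavior is an important precursor to action", so the article itself separates readiness from the act.

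Table 2 has the intervention GP hold at least two ACP conversations, at which the SDM may be present. Patients without an SDM are prompted to consider who could take the role, and the GP completes a template after each conversation. For the comparator (Control: care as usual), "The control group will also not feature the two planned consultations dedicated specifically to discussing ACP"; the topic may still come up spontaneously. The Blinding section states that GPs and patients know their arm.

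Under Recruitment (SDMs), the research assistant (RA) uses a script that "asks whether the patient has formally appointed someone, and if not, who may be able or willing to fulfill this role". Table 3 does not list this question as an outcome measure.

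**The concern.** The only listed source that plainly addresses the event after randomization is the GP. What a GP knows about a patient's SDM depends on whether they have talked about it, and the intervention consists largely of arranging that talk. The intervention may thus raise the number of appointments and also the share of appointments that the GP can report. A difference between arms in GP-reported appointment mixes the two.

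The patient-side source does not clearly separate them. The readiness item belongs to the instrument that supplies the patient primary outcome, so an effect on it partly repeats the primary result. The article does not show whether any of its response options records a completed appointment.

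At stake is the interpretation of one secondary outcome. A difference in favour of ACP-GP could be read as more patients with a formally appointed SDM when part or all of it is better-informed GPs.

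**Working it through.** The article gives no expected appointment rate and no rate of GP awareness, so there is no figure of its own to reproduce. The check compares how each arm's reporter comes to know of an appointment and then illustrates the size with assumed values.

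**Who can know what**

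| | Intervention | Control |
|---|---|---|
| Planned ACP conversations with the GP | at least 2 | none |
| SDM choice raised by design | yes | no |
| Structured template after each conversation | yes | no |
| GP aware of allocation | yes | yes |
| Direct patient report of appointment listed at T1, T2 | no | no |

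**Effect on a comparison at T1.** Let p be the true proportion with an appointed SDM, equal in both arms, and let s_I and s_C be the proportions of those appointments known to the GP. Assume no false positive reports. GP report then shows p·s_I against p·s_C, a false difference of p(s_I − s_C). Assumed: p = 20–40%.

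| Awareness (I vs C) | p = 20% | p = 30% | p = 40% |
|---|---|---|---|
| 90% vs 70% | 18 − 14 = 4 points | 27 − 21 = 6 points | 36 − 28 = 8 points |
| 90% vs 50% | 18 − 10 = 8 points | 27 − 15 = 12 points | 36 − 20 = 16 points |
| 80% vs 80% | 0 | 0 | 0 |

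**Does the T0 measurement remove this?** No. T0 precedes randomization, so expected awareness is the same, s_0, in both arms. Suppose no patient appoints anyone during the trial. If control awareness stays at s_0 and intervention awareness rises to s_I, the reported change is p(s_I − s_0) in the intervention arm and 0 in control. With p = 30%, s_0 = 50% and s_I = 90%, this is 0.30 × 0.40 = 12 points of apparent new appointments, all of them old ones discovered in the conversations.

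**Chance of a false positive.** Secondary endpoints are tested at two-sided 5% once a primary effect is shown, which is nominally 2.5% in the direction of the intervention. Take a normal approximation for two proportions, with a = p·s_I, b = p·s_C, their mean m, and effective n per arm:

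Φ{ [a − b − 1.96·√(2m(1−m)/n)] / √([a(1−a) + b(1−b)]/n) }

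The article's ICC of 0.04 gives n = 54/(1 + 2×0.04) = 50 for the full 54 patients per arm (3 per GP). For 36 per arm (18 GPs with 2 patients each), n = 36/1.04 = 34.6.

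- 90% vs 50%: from 16% (p = 20%, 36 per arm) to 43% (p = 40%, 54 per arm).
- 90% vs 70%: from 7% to 13% over the same range.
- Equal awareness: 2.5%.

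Worked case, p = 40%, 90% vs 50%, n = 50: a = 0.36, b = 0.20, m = 0.28. The numerator is 0.16 − 1.96×0.0898 = −0.016 and the denominator is 0.0884, giving Φ(−0.18) = 0.43.

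**The case against.** **Table 3 is condensed.** The documents row lists GP report yet names only the patient as completer, so the cells are not full specifications. A missing entry is weak proof that no such question is asked. This is fair, but the two adjacent rows differ on exactly this point, and the article fixes the sources as they stand.

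**Patient data may already capture appointment.** The item concerns signing official papers, so a signed appointment might be counted under new ACP documents. Patients also state at T0 whether they have earlier advance directives. This is possible, but the article does not define ACP documents, and it lists appointment as a separate outcome.

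**Other data help.** GPs in both arms report at T1 on conversations, topics and attendance, and patients complete a T1 questionnaire on ACP conversations. Control patients continue to see their GP, and control GPs are asked the question too. These data help in judging unequal awareness but do not remove it.

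**Patient report is not clean either.** Patients are unblinded, and those with the workbook may understand formal appointment differently. This stands as a limit of the fix.

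A reader might go further than the text allows in three ways:

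- That readiness replaces the event. It does not, because GP report addresses the event. Nor can the item be called purely an attitude, since its response options are not shown.
- That intervention GPs are certain to know of more appointments. This is a well-supported inference, not a stated fact.
- That the outcome cannot be assessed without bias, or that a minimum bias can be given. No awareness rates are reported, and with equal awareness the bias is zero.

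**Conclusion.** The point holds as a weakness of measurement in one secondary outcome. The appointment row lists no direct patient report. The listed source that addresses the event is an unblinded GP whose knowledge plausibly depends on allocation, and measuring at T0 does not correct this. The likely direction favours the intervention.

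The magnitude is unknown. The figures of 4–8 and 8–16 points rest on assumed equal true rates of 20–40%, assumed awareness and no false positive reports. The false-positive chances also borrow the ICC given for the patient sample size.

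The protocol labels this outcome exploratory, and neither primary outcome nor the conclusion on effectiveness at T1 depends on it. The change is worth making because it is cheap.

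**What to change.** In the Table 3 row on SDM appointment, add a direct yes/no patient report of formal appointment, using the question already in the RA's recruitment script. Ask it in the same words in both arms at T0, T1 and T2, and name it as the lead source for this outcome. Report GP report and the readiness item separately, as supporting measures.

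The cost is one extra item on questionnaires already given at those three times, plus a table edit. The remaining weakness is self-report by unblinded patients: there will be some misreporting, and it may not be fully equal between arms. But the patient's knowledge of the appointment does not depend on a planned GP conversation.
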